# Effect of including fitness testing in preventive health checks on cardiorespiratory fitness and motivation: study protocol of a randomized controlled trial

**DOI:** 10.1186/1471-2458-14-1057

**Published:** 2014-10-10

**Keywords:** Health examination, Cardiorespiratory fitness test, Exercise test, Cardiorespiratory fitness, Maximum oxygen uptake, Physical activity, Health behaviour, Motivation, Intention, Self-rated health

## Abstract

**Background:**

Preventive health checks may identify individuals with an unhealthy lifestyle and motivate them to change behaviour. However, knowledge about the impact of the different components included in preventive health checks is deficient. The aim of this trial is to evaluate whether including cardiorespiratory fitness testing in preventive health checks 1) increases cardiorespiratory fitness level and motivation to change physical activity behaviour and 2) reduces physical inactivity prevalence and improves self-rated health compared with preventive health checks without fitness testing.

**Methods/Design:**

An open-label, household-cluster, randomized controlled trial with a two-group parallel design is used. The trial is embedded in a population-based health promotion program, “*Check your Health Preventive Program*”, in which all 30–49 year-old citizens in a Danish municipality are offered a preventive health check. In each arm of the trial, 750 citizens will be recruited (1,500 in total). The primary outcome is cardiorespiratory fitness level assessed by submaximal cycle ergometer testing after one year. An intermediate outcome is the percentage of participants increasing motivation for physical activity behaviour change between baseline and two-weeks follow-up assessed using the Transtheoretical Model´s stages of change. Secondary outcomes include changes from baseline to one-year follow-up in physical inactivity prevalence measured by a modified version of the questions developed by Saltin and Grimby, and in self-rated health measures using the Short-Form 12, Health Survey, version 2.

**Discussion:**

This trial will contribute to a critical appraisal of the value of fitness testing as part of preventive health checks. The conduction in real-life community and general practice structures makes the trial findings applicable and transferable to other municipalities providing support to decision-makers in the development of approaches to increase levels of physical activity and improve health.

**Trial registration:**

ClinicalTrials.gov Identifier: NCT02224248. Registered 8 August 2014.

## Background

Changing an unhealthy lifestyle improves health and reduces morbidity [1]. Motivation is a key component in initiation and maintenance of lifestyle changes [2]. Identifying and motivating individuals with an unhealthy lifestyle to change behaviour may be achieved through preventive health checks as already implemented in some countries [3–5]. However, knowledge about the impact of individual components included in preventive health checks is deficient. Consequently, the most effective composition of preventive health checks remains unknown.

In a Danish municipality, the *Check your health preventive program* was recently initiated, offering preventive health checks to all 30 to 49 year-old citizens [4, 6]. This program provides the unique opportunity to evaluate single components of a preventive health check in a real-life setting. Only few previous studies have included cardiorespiratory fitness (fitness) testing in a preventive health check [7, 8]. Fitness level is associated with multiple health benefits such as improved cardio-metabolic profile and reduced risk of cancer, diabetes, and depression [9]. The primary determinant of fitness is physical activity behaviour [10]. Performing a fitness test may raise individual awareness of one´s actual fitness and lead to physical activity behaviour changes. The conception that measurement itself may influence behaviour is well-established and has already been applied in some physical activity promotion trials [11]. “Measurement reactivity” and “mere measurement” effect are some of the terms used to describe the phenomenon [12]. Increasing awareness and motivation have been proposed as explanations for the effect [13, 14]. A Danish report documented health status as being the most important motivational factor among physically inactive adults [15]. Conjoined, the realization of poor fitness and unfavourable health status may operate synergistic in motivating physically inactive individuals to change physical activity behaviour. Investigating the effect of including fitness testing in a preventive health check is therefore intriguing.

Our aim is to investigate the effect of including fitness testing in preventive health checks on 1) fitness level and motivation for changing physical activity behaviour and 2) changes in physical inactivity prevalence and self-rated health. We hypothesize that fitness testing as part of preventive health checks compared to preventive health checks without fitness testing 1) increases fitness level assessed after one year and the percentage of participants increasing motivation to change physical activity behaviour assessed after two weeks, and 2) reduces physical inactivity prevalence and improves self-rated health scores during the one-year study period. The study protocol conforms to the CONSORT Statement for randomized trials of non-pharmacological treatment.

## Methods

### Trial design

The trial is as an open-label, household-cluster randomized controlled trial with a two-group parallel design. The trial is nested in the ongoing health promotion program entitled *Check your Health Preventive Program* (CHPP) [4, 6]. The CHPP is carried out during the five-year period 2012 to 2017. The present trial will be conducted in 2014 to 2016, including a follow-up period of one year.

### Participants and settings

In the CHPP, all citizens living in the municipality of Randers aged 30–49 years per 1^st^ of January 2012 (n =26,216) were identified in the Danish Civil Register, in which a permanent and unique identification number is assigned to every Danish inhabitant at birth and to residents on immigration. The identified population was randomized into five equal groups, one for each year of the CHPP [6]. Citizens randomized for group three (n =5,249) are considered eligible for the present trial (Figure 1). A single exclusion criterion for not receiving an invitation in the CHPP is terminal illness as reported by the general practitioners (GPs) [6]. Invitations are dispatched continuously by mail and include information about the CHPP and a prefixed appointment for a health check. This appointment can be accepted, altered or rejected via phone or internet. If no response, a reminder with a new appointment is sent after 7 days and again after three weeks [6]. Randomization in the present trial is conducted prior to dispatching the invitations. The enrolment proceeds continuously, until 750 participants in each arm of the trial have received a health check and consented for data to be used scientifically. Health checks and health behavioural courses will take place at Randers Health Centre (RHC) and health consultations at the citizen´s GP.

**Figure 1 Fig1:**
[figure not shown]
**Flow of participants in the CHPP and the present trial.** R_1_: Randomization by household to one of the five years in the CHPP. R_2_: Randomization by household to intervention or control in the present trial prior to dispatching the invitations. Invitation and inclusion proceed continuously until 750 participants in each arm of the trial have received a health check and consented for data to be used scientifically. Abbreviations: CHPP: Check your Health Preventive Program.

### Intervention group

As part of the CHPP, the intervention group will answer a questionnaire and receive a preventive health check with fitness testing (Figure 1). Subsequent follow-up actions will proceed according to risk profile and individual choices (see Follow-up by risk).

### Questionnaire

Prior to the health check, a web-based questionnaire regarding physical activity level [16], motivation for changing physical activity behaviour [17], self-rated health [18], smoking habits [19] and alcohol risk behaviour [20] will be answered. Participants have the opportunity to answer the questionnaire at the RHC, if support is needed.

### Fitness testing

Fitness level will be assessed using a modified version of the Astrand submaximal cycle ergometer test [21] (Monark 939 E Pendulum Ergometer, Monark Exercise AB, Sweden) with a workload of 75 watt for women and 100 watt for men. Pedalling frequency is set between 60–70 rounds per minute. Heart rate will be measured continuously (polar T31 coded transmitter, Polar, Denmark) and recorded at 5.5 minutes, if participants achieve a steady-state pulse within a target interval of 120–170 beats/min. Steady state is defined as two consecutive heart rate recordings within 5 beats of each other [22]. If the target interval is not reached after 2 minutes of cycling, the workload will be increased with 35 and 50 watt for women and men, respectively. The test will proceed until a steady-state is reached. Fitness level will be estimated from the recorded heart rate and workload standardized to age and sex [21] (Monark 939 E Analysis Software, Version 3.0.9, Monark Exercise AB, Sweden). Blood pressure above 180/110 mmHg is considered a contraindication for performing the test. Moreover, the use of pacemaker or beta-antagonists results in exclusion from fitness testing due to unreliable heart rate responses [23].

### The health check

In addition to fitness testing, the health check will include assessment of body weight and height, waist circumference, systolic and diastolic blood pressure, biochemical measures (lipid profile, glycated haemoglobin (HbA1c)), and lung function. Moreover, cardiovascular disease a risk score is calculated. The health check, including all measurements, is described in detail elsewhere [6].

### Follow-up by risk

At the end of the health check, the results are presented in a personalized health profile leaflet, which includes recommendations for follow-up actions according to the risk-profile. Participants can either be referred to (a) a health-promoting consultation in general practice, (b) targeted health behavioural programs at RHC, or (c) no further follow-up. Participants advised to consult their GP are those with abnormal values of blood pressure, biochemical measures, lung function, self-rated health, including mental health, and alcohol risk behaviour [6]. Participants offered referral to behavioural programs are those with high body mass index and waist circumference, smokers, and physically inactive individuals. Participants referred to general practice can be referred to these programs by their GP. Participants with no risk factors receive no further follow-up. The stratification-algorithm and the behavioural programs are previously described [6].

### Control group

As part of the CHPP, the control group will answer the same questionnaire as the intervention group and receive an identical preventive health check *without* fitness testing (Figure 1). Subsequent follow-up procedures are equal to those described for the intervention group.

### Standardization and education of health care professionals

The health check will be conducted by health professionals trained in all measurement procedures and risk communication to ensure standardization and quality [6]. Execution of the health check is further standardized by a written protocol, to which adherence is checked continuously. As a part of the CHPP, the GPs received education in physical activity promotion and shared decision-making [6]. There is no standardization of the GPs handling of the results from the health check.

### Randomization and implementation

Randomization is handled by a data-manager with no scientific involvement. The eligible population for this trial was defined by the CHPP randomization, which was performed on clusters defined by households based on addresses obtained from the Danish Civil Register [6]. Using the same index individual per household, citizens randomized to group three in the CHPP will be further randomized by household to either intervention or control in the present trial (Figure 1). In practice, every second week will be scheduled for intervention group participants and the remaining weeks for control group participants. Group assignment will be maintained regardless of changes in the initially assigned appointment. Implementation and management of the booking-system is handled by a data-manager. The intervention, the outcomes, group assignment, and the future outcome assessments in this trial are unrevealed in the invitation for the CHPP. The health behavioural courses and the health consultations will be carried out unblinded due to the real-life setting. At the one-year follow-up, the personnel assessing the outcomes will be independent and blinded to group allocation.

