### Outcome assessments

The intervention group and the control group will receive identical outcome assessments at two evaluation contacts. All participants will receive a questionnaire regarding motivation for changing physical activity behaviour two weeks after the health check and will be invited for fitness testing and asked to fill out a questionnaire after one year (Figure 1).

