### Intermediate outcome

#### Motivation for physical activity behaviour change

Motivation for physical activity behaviour change will be operationalized by conceiving *intention* (to adopt a specific behavioural criterion) as a motivational construct. The Transtheoretical Model will compose the theoretical framework using the stages of change [17]. Stages of change conceptualize behaviour change as a progression through a series of five stages: *precontemplation* (*no intention* to engage in regular physical activity within the next six months), *contemplation* (*intention* to engage in regular physical activity *within the next six month*), *preparation (intention* to engage in regular physical activity *within the next 30 days), action* (regular physical activity behaviour initiated), and *maintenance* (regular physical activity has been performed for 6 month or more) [17, 24]. The three initial stages represent the motivational phase, in which intention is thought to increase [17]. We will consider progression from one of these three stages at baseline to a higher stage assessed two weeks after the health check as a motivational increase [17] and the percentage of participants increasing motivation as the specific outcome. Participants will stage themselves into one of the five stages according to their intention to engage in regular moderate physical activity defined as occurring on 5 or more days a week for at least 30 minutes (or 3 × 10 minutes) [23]. Moderate intensity is defined as producing increased heart rate, but being able to converse.

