### Statistical methods

Statistical analysis will be performed using STATA 12.0 software. Continuous variables are presented as mean ± standard deviation and categorical variables as absolute numbers and relative (%) frequencies. In the comparative analyses Student´s t-test will be used, when comparing means or changes in means of continuous variables and Chi^2^-test or Fisher’s exact t-test, when comparing proportions for categorical variables. Analyses will be adjusted for baseline physical activity. Stratified analyses will be performed on sex and age groups and analysis of motivation will be performed on a subgroup comprising precontemplaters, contemplaters, and preparators at baseline. All analyses will follow the intention-to-treat principle [28]. If appropriate, multiple imputation methods will be applied [29] (using data from social and medical national registries coupled with health check data), and sensitivity analyses will be performed. Moreover, the potential effect of clustering by the GPs will be investigated. The statistical significance level is set at p <0.05.

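### Health checks run in alternating single-arm weeks, yet the two-week motivation comparison treats participants as independent and names only GP clustering; its p-value is too optimistic if weeks differ irregularly

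*Protocol article*

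**What the plan says.** All places are in the Methods of the protocol article.

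- **Unit of randomization** (Randomization and implementation): citizens in group three of the parent programme "will be further randomized by household to either intervention or control in the present trial".
- **Delivery** (same section): "every second week will be scheduled for intervention group participants and the remaining weeks for control group participants". On rebooking: "Group assignment will be maintained regardless of changes in the initially assigned appointment".
- **Outcome timing** (Outcome assessments): "All participants will receive a questionnaire regarding motivation for changing physical activity behaviour two weeks after the health check".
- **Endpoint** (Motivation for physical activity behaviour change): progression from one of the three early stages to a higher one, with "the percentage of participants increasing motivation as the specific outcome".
- **Analysis** (Statistical methods): a Chi2 or Fisher test is used "when comparing proportions for categorical variables", and "analysis of motivation will be performed on a subgroup comprising precontemplaters, contemplaters, and preparators at baseline". Analyses are adjusted for baseline physical activity, and significance is set at p<0.05. On clustering the section says only that "the potential effect of clustering by the GPs will be investigated".

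The Sample size section also allows for GP clustering alone (46 practices, ICC 0.05). Week appears in neither section.

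**The concern.** Under this schedule, everyone booked for a given week belongs to one arm and has the health check under that week's conditions. Motivation is the outcome measured closest to the visit, so it is the one most exposed to whatever was particular to that week. A week effect is shared by a batch of participants in one arm, with no counterpart in the other arm that same week.

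GP clustering does not stand in for this. Because households are randomized, one practice can have patients in both arms, so practice effects largely cancel in the arm difference. Irregular week effects do not.

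A test on individuals leaves the between-week part out of its standard error. If that part is not zero, the p-value, and any interval reported with it, overstates the evidence, and an effect on motivation could be claimed too readily.

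**Working it through.** **1. The plan's own figure.** No sample size or power is given for motivation. The 1,500 is for the categorical fitness outcome. It cannot be reproduced uniquely, because the control prevalence is not stated. It is consistent with, for example, 25% against 15%:
- n = 250 per arm before inflation
- GP design effect = 1 + (1,050/46 − 1) × 0.05 = 2.09, where 1,050 = 1,500 × 0.7
- 250 × 2.09 = 523 per arm; 523/0.7 = 748 per arm; total 1,496

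The figure is not shown to be wrong. It contains no week component.

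**2. Inputs for the week effect.**
- From the article: 750 per arm, alternating single-arm weeks, alpha 0.05 (taken as two-sided).
- Assumed: recruitment fills one programme year (52 weeks, 26 per arm), since group three is one of five yearly groups. Then 750/26 = 28.8 participants per week.
- Assumed: half are in the three early stages, so about 14 analysed per week (base case).
- Low variant: 30% of these do not return the two-week questionnaire (borrowing the article's general loss figure), 14.4 × 0.7 = about 10.
- High variant: about 29 per week, if everyone is in the subgroup or recruitment takes half as long.
- Assumed: week ICC 0 to 0.02. The article gives no value.

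**3. Formulas.** With m analysed per week, DE = 1 + (m − 1) × ICC. The standard error is too small by a factor √DE. The true type I error of a nominal 5% test is 2 × [1 − Φ(1.96/√DE)].

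Example, m = 14 and ICC 0.01: DE = 1 + 13 × 0.01 = 1.13; 1.96/√1.13 = 1.84; type I error 6.5%.

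| Week ICC | m = 10 | m = 14 | m = 29 |
|---|---|---|---|
| 0 | 5.0% | 5.0% | 5.0% |
| 0.005 | 5.5% | 5.8% | 6.6% |
| 0.01 | 6.1% | 6.5% | 8.3% |
| 0.02 | 7.1% | 8.1% | 11.7% |

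**4. Check by simulation.** With 26 weeks per arm, an assumed 30% progressing and independent week effects, the individual-level test rejected a true null 6.4% and 8.4% of the time at ICC 0.01 and 0.02 with 375 analysed per arm. With 750 per arm it rejected 8.6% and 12.0%. A t-test on week-level proportions stayed near 5%.

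**5. Slow trends.** When week effects were smooth over time (autocorrelation 0.8), the individual-level test rejected only 5.3% to 6.2% of the time, even with ICC up to 0.05. Neighbouring weeks fall in opposite arms, so a slow trend mostly cancels.

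**6. A trap in the remedy.** Suppose fortnight blocks are fitted and standard errors are clustered by week. Each block holds one week per arm, so the two week residuals in a block are equal and opposite. The variance estimate then comes out at about half the true value, and the rejection rate under no effect is about 2 × [1 − Φ(1.96/√2)] = 2 × [1 − Φ(1.386)] = 17%. Simulation gave about 17% as well. That is worse than the plain test.

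**The case against.** The strongest reply has five parts.

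- **Standardized delivery.** Health professionals are trained, and a written protocol with continuous adherence checks governs the visit. This makes a large staff-related week effect less likely. It does not remove holidays or local events.
- **Change within person.** The endpoint is progression from a stage recorded before the check, so conditions common to both questionnaires may partly cancel. Effects of the visit itself do not.
- **Rebooking.** Appointments can be altered, and the article does not say whether rebooked people attend a week of their own arm. If some do not, attended week is not fully nested in arm and the effect is diluted. This is a reason to cluster on attended week.
- **Scope.** The article is condensed, and an analysis plan that is not shown may already deal with weeks. That is possible. The article does, however, fix a test and name a cluster, and that stated choice does not match its own delivery schedule.
- **Unit.** Week was not the randomized unit. That is correct: the point concerns variance arising in delivery and does not invalidate the allocation. Household, which is the randomized unit, is also absent from the analysis section, but that is a separate matter.

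A reader might infer more than the text supports. One inference is that season, or the municipal health initiatives mentioned under Strengths and limitations, distort the comparison. The alternation largely balances slow trends, and the article presents those initiatives as attenuating the effect, not as weekly shocks. Another is that the test is known to be too liberal. With a week ICC of zero nothing changes, and the article does not tell us the ICC. Nor does the argument extend to the one-year fitness outcome.

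**Conclusion.** The point holds in conditional form. Scheduled week is nested in arm, the motivation outcome follows directly from that week's visit, and the stated test leaves out between-week variance while naming a cluster that crosses arms. The direction is clear: if weeks differ irregularly, the p-value is too small.

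The size is not derivable from the article. It rests on three assumed quantities: week ICC, number of weeks and subgroup size. Over the ranges in the table the true type I error runs from 5% to about 12%. With 10 to 14 analysed per week and a non-zero ICC up to 0.02, it is about 5.5% to 8%. This is a modest effect on an intermediate outcome, and it is worth correcting mainly because correction is cheap.

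**What to change.** In Statistical methods, replace the plain Chi2 or Fisher comparison of the motivation percentage with one of these, decided in advance:

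- a regression model for progression with a random effect for attended health-check week and the planned adjustment for baseline physical activity; or
- a comparison of week-level proportions, optionally as paired differences between the two weeks of each fortnight, with baseline physical activity adjusted for before the proportions are formed.

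If fortnight blocks are used, take the standard error from the fortnight-pair differences. Do not combine fortnight blocks with week-clustered standard errors, which are far too small. Add one sentence saying whether rebooked participants attend a week of their own arm.

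**Cost:** analysis wording only, with no change to design, sample size or conduct. Attended week should be available from the booking system that the article describes. The downside is a slightly wider interval: about 6% wider at ICC 0.01 and 12% wider at ICC 0.02 with 14 per week (√1.13 = 1.06; √1.26 = 1.12).
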